#### Statistical and sample size calculations

Descriptive statistics will be shown as mean with standard deviation or median with minimum and maximum values for continuous and ordinal variables where appropriate. Number with percent will be shown for categorical variables.

The primary outcome is clinical index at 24 h. The time is chosen since our experience is that most infants will remain at hospital at that time and an effect should have been shown. The effect of the individualised physiotherapy intervention, the non-individualised intervention, and a control group receiving standard care on clinical index at 24 h will be assessed by an ANCOVA model with adjustment for baseline clinical index, and post hoc test for the different group combinations will be performed.

The secondary outcomes, including clinical index at 20 min, will first be assessed by an overall test and if the overall test is shown significant post-hoc tests will be performed. A *p* value below 0.05 will be considered significant for the overall test. Continuous and ordinal variables will be assessed by ANCOVA model with adjustment for baseline values where possible, ANOVA, or Kruskal-Wallis test, with *t* test or Mann-Whitney *U* test as post hoc tests, where appropriate. Categorical variables will be assessed by Fisher’s exact test. Explorative subgroup analyses by gender will be performed. To increase the knowledge about what time the infants will recover, data are collected every 3 h. We will analyse the time the infants recover by means of Fisher’ exact test and Kaplan-Meier analysis. IBM SPSS Statistics 24, or higher, Windows (IBM Corporation, Armonk, NY, USA) will be used to perform the statistical analyses.

The primary analysis will include all participants with available outcome data at 24 h. Drop-outs will not be included in this analysis. A dataset with the imputed values might also be analysed. Simple imputation, mean of the value before and after the missing value or last value carried forward from the assessment three hours earlier, will be performed if data is missing at hour 24 and the patient is still at hospital. If an infant will be discharged from the ward before hour 24, that participant will be excluded from this analysis and will be analysed in the same way as the other potential drop-outs.

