The sample size is calculated on a two-sided two sample *t* test with equal variance. The mean difference that we want to be able to detect in clinical index at 24 h is 2. A previous pilot study (unpublished material) has shown that the standard deviation is approximately 2.8. The power probability for the test is 0.80, and to be able to correct for the three primary tests, comparing the individualised physiotherapy intervention, the non-individualised intervention, and a control group receiving standard care with each other, the type I error probability in the calculation is 0.016, confidence interval 0.95. To be able to detect the difference, 43 evaluable patients in each group is needed. The calculation is performed in SAS Enterprise Guide 6.1 for Windows (SAS Institute Inc., Cary, NC, USA). Incomplete observations and drop-outs are expected to amount to about 20%. Thus, a total of 162 patients are needed to be included in the study. The drop-outs will be analysed according to age, possible viral infection, gender, allocation group, and severity of illness at admission to the ward (saturation, respiratory rate and heart rate or more data if collected). We plan to perform an interim analysis of the data obtained after inclusion of 50% of the estimated sample size in order to check the assumptions about the standard deviation and recalculate the sample size. In that analysis, we will also be able to address possible safety concerns in the study, although we do not anticipate any harmful outcome. That analysis will be performed by a statistician independent of the study, and the result will only be presented to the research group at this stage if any harmful outcome will be detected in the intervention groups, such as significant inferior outcomes in the intervention groups compared to the control arm. Further instructions will be discussed by the trial team before the interim analysis.

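### The three primary pairwise tests are sized at 0.016 each but have no stated level or gate in the analysis; with three groups, gating them on the overall test at 0.05 controls error with more power

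*Protocol article*

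**What the plan says.** All the relevant text is in the Protocol article, section Statistical and sample size calculations.

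- **Sizing.** The calculation is for a "two-sided two sample *t* test with equal variance". A reduced level is used "to be able to correct for the three primary tests" of the three arms with each other, and the sentence ends "the type I error probability in the calculation is 0.016, confidence interval 0.95". The result is 43 evaluable infants per group, and 162 in total after about 20% drop-out.
- **Primary analysis.** The 24 h clinical index is analysed by ANCOVA adjusted for the baseline index, and "post hoc test for the different group combinations will be performed". This sentence carries no level, no adjustment method and no condition on the overall group test.
- **Secondary outcomes.** The next paragraph makes post hoc tests conditional on a significant overall test, for which a p "value below 0.05 will be considered significant for the overall test".

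**The concern.** The article states a correction, a gate, a level and an interval, but they do not add up to one decision rule for the primary outcome. The secondary outcomes have a more explicit rule than the primary one.

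This matters because the section Interventions says that the non-individualised treatment would be judged sufficient if it shows a statistically and clinically relevant improvement over control. That conclusion rests on one pairwise test, and the analysis text does not say at what level, or after what gate, it is made.

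The interval adds to the doubt. If 0.95 means an individual interval for each difference, it does not correspond to a test at 0.016.

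There is also a question of efficiency. The plan already uses an overall-test gate for the secondary outcomes. With exactly three groups, the same gate would protect the primary comparisons at less cost in power than a fixed 0.016 for each.

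**Working it through.** **Inputs, all from the sample-size text.** "The mean difference that we want to be able to detect in clinical index at 24 h is 2"; "the standard deviation is approximately 2.8"; "The power probability for the test is 0.80"; level 0.016 per test, two-sided; 43 evaluable per group; drop-out 20%.

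**1. The plan's own figure.**
- Three tests: 0.05/3 = 0.0167, entered as 0.016; 3 × 0.016 = 0.048.
- Standard error of a difference at n = 43: 2.8 × √(2/43) = 0.604.
- Non-centrality: 2/0.604 = 3.31, with 2 × 43 − 2 = 84 degrees of freedom.
- Exact noncentral-t power at 0.016: 0.801. The smallest n reaching 0.80 is 43, as stated.
- 43/0.8 = 53.75, rounded up to 54 per group; 3 × 54 = 162, as stated.
- For comparison, an uncorrected 0.05 would need 32 per group, and 43 per group would give power 0.906.

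**2. Interval against test.**
- 95% half-width: 1.989 × 0.604 = 1.20 points.
- 98.4% half-width, the match for 0.016: 2.459 × 0.604 = 1.48 points.
- An observed difference between about 1.20 and 1.48 points would exclude zero on an individual 95% interval yet fail at 0.016. With a true 2-point difference this happens in about 0.906 − 0.801 = 0.105, or roughly 10% of trials.

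**3. Why the gate works with three groups.** If any two of the three pairwise null hypotheses are true, all three means are equal. The only joint hypothesis is therefore the overall one. Testing it at 0.05, and then each pair at 0.05, is a closed procedure that holds family-wise error at 5%.

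**4. Simulation.** Three groups of 43, SD 2.8, pooled variance (126 degrees of freedom), 400,000 runs, no credit for baseline adjustment.

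| Rule for the three pairs | Family-wise error, all means equal |
|---|---|
| 0.05 each, no gate | 12.1% |
| 0.016 each, no gate | 4.2% |
| Overall test at 0.05, then 0.05 each | 5.0% |

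When two arms are equal and the third differs by 2 points, the gated rule falsely rejects the equal pair in 5.0% of trials.

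| True means | Power for a 2-point pair, 0.016 each | Gated |
|---|---|---|
| 0, 1, 2 (third arm midway) | 81% | 84% |
| 0, 0, 2 (third arm equal to one of the pair) | 81% | 89% |
| 0, 2, 4 | 81% | 91% |

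**5. What the gate costs.** An unadjusted 95% interval can exclude zero when the overall test fails. For the 2-point pair this occurs in about 7% of trials with the third arm midway, about 2% with the third arm equal to one of the pair, and essentially never with means 0, 2, 4. With no effect at all, at least one interval does so in 12.1% − 5.0% = about 7% of trials.

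**The case against.** The case for leaving the text alone has several parts.

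- **The intent to correct is stated.** The sizing text names the three pairwise tests as primary, and gives a level and its reason. A reader might infer that the primary claim carries a 12% family-wise error. The documents do not support that. The 0.05 belongs to the overall test in the secondary-outcome paragraph, and uncorrected pairwise tests at 0.05 would go against the stated intent. That no gate applies is itself inferred from silence.
- **The 95% interval is not in the analysis text.** A reader might infer that the plan pairs 95% intervals with 0.016 tests. The figure occurs only in the sizing sentence. Because 3 × 0.016 = 0.048, it may mean a joint 95% level for the family. It is an ambiguity, not a proven contradiction, and the roughly 10% disagreement applies only under the individual-interval reading.
- **The power cost is not pointless.** A reader might infer that 0.016 wastes power. For ungated tests it is what brings family-wise error from 12.1% down to 4.2%, and the trial keeps its planned power. The cost is avoidable only if a gate is adopted.
- **The level may be stated elsewhere.** The statistical analysis plan was not available. The absence of the 0.016 level from the analysis sentence is not, taken alone, a fault.
- **The gate has its own drawbacks.** Pairwise claims come to depend on an overall test, and unadjusted intervals can still disagree with decisions.

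All of these stand. None removes the practical point that the plan already contains a gate which, for three groups, gives valid control with more power in every configuration tried.

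**Conclusion.** The correction at 0.016 is valid and the sample size reproduces. What remains is a primary decision rule that the article does not state in one piece, an unclear interval level, and a better rule available at almost no cost. The gain is about 3 percentage points of power with the third arm midway, 8 with the third arm equal to one of the pair, and 10 with means 0, 2, 4. Family-wise error moves from 4.2% to 5.0%.

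These figures assume normal errors, equal variances, 43 evaluable infants in every group and a residual SD of 2.8. Baseline adjustment would lower the residual SD and raise power under either rule. This is a worthwhile improvement, not an error that invalidates the trial.

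**What to change.** For the primary outcome, state that the group effect in the ANCOVA is tested at 0.05 and that, only if it is significant, the three baseline-adjusted pairwise contrasts are each tested at two-sided 0.05. Describe 0.016 in the sample-size text as a conservative planning value and keep 162 infants. Say that decisions rest on the gated tests, and label the pairwise 95% intervals as unadjusted, because they can exclude zero when the overall test fails.

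If the sponsor prefers 0.016 per comparison, write that level into the analysis sentence and report 98.4% intervals. In either case, say what the 0.95 in the sample-size sentence refers to.

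The cost is a few sentences, with no extra infants or data. The price of the gated rule is that no pairwise claim can be made when the overall test is not significant.

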#### Data management

Data from all assessments will be decoded and stored in an external hard drive that is kept in a safe to which only the researchers responsible have access. The hard drive has no connection to the Internet. The data from the paper protocols will be manually entered onto the database by the primary investigator ([name]). The accuracy of the data in randomly chosen protocols will be double-checked by two other researchers in the group. During the period of entering data, the hard drive will be regularly backed-up to a USB memory, which will also be kept in a safe. All files will be saved for at least 10 years after completion of the study. The data will be disseminated by publication in scientific journals.

## Discussion

Infants hospitalised due to acute respiratory failure caused by bronchiolitis and pneumonia is a recurring group of patients in paediatric departments. Hospitalisation is a burden for both the families and for society, and possible treatments that reduce the need for hospitalisation by reducing the work of breathing and increase the general condition of the infant are called for, as well as finding treatments that alleviate the current situation for these infants during hospitalisation.

Our study focuses on a possible effect of an individualised physiotherapy intervention and a non-individualised intervention compared to the standard care (without additional movements).

We chose to include infants without previously diagnosed respiratory and cardiac diseases, in order to evaluate the effect of physiotherapy in a homogenous group of patients, in a real-life setting in two departments.

We chose the individualised physiotherapy intervention because that is the most common physiotherapy treatment method in Sweden [22] and previously not evaluated. The non-individualised physiotherapy intervention can be used by the nursing staff and is less time-consuming and often used, while the control group will receive treatment as recommended in earlier studies [4, 40].

Blinding a physiotherapy study is difficult. In some studies, this problem was solved by bringing all infants to a closed room to do the physiotherapy intervention or nothing, without the parents and nursing staff knowing what was done [5, 8, 19]. In our study, we wanted to evaluate the commonly used methods that often involve parents’ actions, and blinding of parents to participants, care providers, or assessors was not possible due to the nature of the intervention. To minimise possible bias, one person will perform the intervention and another person will evaluate the result of the different interventions (make the assessment). The statistician involved in the analyses will be blinded.

Block randomisation was chosen to ensure equal numbers of participants in the three groups over time as this can compensate for possible differences in treatment in the two sites, but even for possible changes in the surroundings over time (learning curve, change of staff or temporary severity of the infection). A drawback with equal numbers in the three groups is that exclusions from the physiotherapy intervention group is more likely to be made than from the other groups due to absence of a physiotherapist on occasions, for example at nights and absence due to leave. We have, however, calculated generously on the drop-out rate to compensate for this, and the drop-outs will be closely analysed as described earlier.

There is a need for an easy and clinically relevant scoring system for assessing infants with breathing difficulties in hospitals. Our primary outcome is a clinical index that the research group constructed, based on the factors that determine whether the infant needs hospitalisation [28]. The items in the clinical index were chosen because of their clinical implication. They are based on objective values and are therefore not likely to differ between different assessors. Similar outcome measures were also used by Rochat et al. [9].

For secondary outcomes, we included the Wang score, since it is often used in other studies of infants with acute respiratory infections [5, 8, 19] and has been validated. Furthermore, the parents’ report on the infants’ well-being and eating ability was included. The parents have unique knowledge of their own child, which we thought could make a valuable addition to the nursing staff’s assessment. The parents’ report has not, to our knowledge, been used before in studies of infants with breathing difficulties in hospitals. These two scores were constructed by the research group for this purpose and are not validated for this use. The numeric rating scale 0–10 has been used before to assess different symptoms although not validated for this, like well-being, depression, fatigue, and anxiety [38], and by using it in this study, we hope to gain at least some information about the parents’ assessment of their infant’s general well-being. The outcome measures were chosen with the aim to detect many different types of change in the infants’ status.

The result from this RCT will add new knowledge about the effect of physiotherapy interventions on infants hospitalised with acute breathing difficulties due to respiratory infections. It may also contribute to an increased understanding of how to perform studies on infants in a clinical setting in hospitals.

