#### Interventions

The position for all infants at baseline is supine on the bed, that is, lying on their backs. Directly following the baseline assessment, there will be 20 min of interventions for the two intervention groups and 20 min of no extra intervention for the controls. All participants will receive the standard care at the ward without limitation, and the participants in the intervention groups will have physiotherapy treatment in addition to the standard care.

*The standard care* at the wards is information to the parents about the importance of fluid intake for their infant, oxygen supplementation, nose drops and suctioning, high nasal flow, inhalations, fluid supplementation, and analgesics, according to need.

The different interventions were chosen based on what is routinely carried out by physiotherapists or nursing staff in hospitals in Sweden [22], including an individualised physiotherapy treatment and a reduced non-individualised treatment. We expect that the individual intervention might be more efficient, but at the same time want to know whether the non-individualised treatment would be sufficient for these patients, indicated by outcomes in the non-individualised group showing a both statistically and clinically relevant improvement compared to the control arm.

In the individualised intervention group, the intervention is minimally given once daily by the physiotherapist, and in the non-individualised intervention group, the intervention is minimally given by the staff once. The randomised treatment, or indeed what will be performed in the control group, will not be monitored, so there might be differences in adherence to the interventions between parents. Our intention, however, is to evaluate the current practice that includes instructions and encouragements to the parents. This attitude is in accordance with a so-called pragmatic RCT, as our intention is to apply the results to the usual care setting [39].

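### The plan allows randomised infants to be excluded from the individualised arm when no physiotherapist is available; the drop-out allowance said to compensate cannot correct the resulting selection bias

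*Protocol article*

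**What the plan says.** All references are to the protocol article.

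- **Discussion.** The article names a drawback of equal group sizes: "exclusions from the physiotherapy intervention group is more likely to be made than from the other groups due to absence of a physiotherapist", with nights and leave as examples. Its answer is: "We have, however, calculated generously on the drop-out rate to compensate for this". It adds that drop-outs will be examined closely.
- **Randomisation.** After parental consent, ward staff open the lowest-numbered envelope. Nothing makes this conditional on a physiotherapist being available.
- **Interventions.** "Directly following the baseline assessment, there will be 20 min of interventions for the two intervention groups". The individualised programme is given by a physiotherapist, the non-individualised one by ward staff. The same section says delivery in the three groups will not be monitored and describes the trial as pragmatic.
- **Statistical and sample size calculations.** The primary analysis is an ANCOVA of the 24 h clinical index, adjusted for baseline index, in infants with 24 h data. Drop-outs are left out, and infants discharged before 24 h are handled in the same way. On the allowance: "Incomplete observations and drop-outs are expected to amount to about 20" per cent, one figure for all arms and all reasons. Drop-outs will be compared on age, virus, gender, allocation group and severity at admission.

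**The concern.** An exclusion that depends on the allocated arm and happens after allocation undoes part of what randomisation provides. Take two similar infants enrolled on the same night. The one allocated to control, or to the staff-delivered programme, stays in. The one allocated to the individualised arm may be removed because nobody can deliver that programme. If infants enrolled at such times differ in prognosis from the rest, the individualised arm is no longer comparable with the other two.

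Two of the three primary comparisons are affected: individualised against control, and individualised against non-individualised. The comparison of non-individualised with control is not. The stated remedy, a larger sample, bears on precision only.

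**Working it through.** **Step 1. The plan's own sample size.** Inputs, all from Statistical and sample size calculations: an equal-variance t test comparing two groups, two-sided; a target difference of 2 points on the 24 h index; an SD taken from a pilot study ("the standard deviation is approximately 2.8"); a target power of 0.80; two-sided type I error 0.016 per comparison.

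Power is the probability that a noncentral t variable with n1 + n2 − 2 degrees of freedom and noncentrality 2 / (2.8 × √(1/n1 + 1/n2)) exceeds the two-sided 0.016 critical value in absolute size.

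- 43 v 43: noncentrality 3.31, critical value 2.46, power 0.801. The stated 43 per group reproduces.
- Inflation: 43 / 0.80 = 53.75, rounded up to 54; 3 × 54 = 162. The stated total reproduces.

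**Step 2. Slack in the allowance.** 54 × 0.80 = 43.2, so the expected 20% loss uses up the allowance. That 20% must also absorb discharges before 24 h and other incomplete observations. If the individualised arm loses more than 20%, it falls below 43.

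**Step 3. Power if that arm loses more.** The article gives no arm-specific rate, so the losses below are assumptions. The comparator is held at 43 evaluable, and baseline adjustment is ignored, as in the plan's calculation.

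| Evaluable, individualised v other | Assumed loss in individualised arm | Power |
|---|---|---|
| 43 v 43 | 20% (plan) | 0.80 |
| 37 v 43 | about 30% | 0.76 |
| 35 v 43 | about 35% | 0.75 |

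If instead the total loss stays near 20% (32 of 162) and 18 of the losses fall in the individualised arm, leaving 36 v 47, power is 0.78.

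**Step 4. Bias.** Suppose a share f of the individualised arm is excluded, and the mean index of those infants differs by g points from that of the retained infants. The retained mean then differs from the full-arm mean by f × g. Sample size does not enter. Here g must be read as the difference that remains after adjustment for baseline index, because the primary model removes the part that baseline explains. Neither f nor g is in the article. Assumed values for illustration:

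- f = 0.2, g = 2: bias 0.2 × 2 = 0.4 points
- f = 0.3, g = 2: bias 0.3 × 2 = 0.6 points

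**Step 5. What such a bias does to the test.** The formula of step 1 is used with the bias in place of the 2-point difference and no true effect (SD 2.8, nominal 0.016). The range covers 30 to 43 evaluable infants in the individualised arm against 43.

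| Residual bias (assumed) | Actual type I error per comparison |
|---|---|
| 0 | 0.016 |
| 0.4 points | about 0.04 |
| 0.6 points | 0.06 to 0.08 |

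At 0.6 points the error is 0.064 with 30 v 43 and 0.076 with 43 v 43. More infants make the false signal easier to detect, so enlarging the trial works in the wrong direction.

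**Step 6. The sections side by side.** Interventions describes a pragmatic trial of current practice with adherence not monitored. Statistical and sample size calculations includes all participants with 24 h data. Read together, these would keep an infant whom no physiotherapist reached. The Discussion treats that same infant as an exclusion to be covered by the drop-out rate. The three sections do not agree.

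**The case against.** **The 20% may already include these exclusions.** The Discussion says the rate was set with them in mind, and the article gives no breakdown. If the individualised arm loses 20% or less in total, 43 remain and power holds. This stands, so the power shortfall is conditional.

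**Baseline adjustment helps power.** The sample size uses an unadjusted t test but the analysis is an ANCOVA. If 2.8 is the unadjusted SD and baseline and 24 h index correlate at 0.4 (both assumptions), the SD becomes 2.8 × √(1 − 0.16) = 2.57, and power is 0.87 at 43 v 43 and 0.83 at 35 v 43. This also stands, and makes power the lesser issue.

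**Baseline adjustment reduces bias, and the trigger is staffing, not the infant's condition.** Nothing in the article says infants enrolled at night are sicker. That limits what can be said about size and direction. It does not remove the problem: adjustment for baseline index deals only with what that index captures, and time of enrolment is not in the model.

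**The problem is disclosed and drop-outs will be compared between groups.** That comparison describes the loss but does not correct it, and its listed factors omit time of enrolment.

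**Stronger readings to avoid.** A reader might infer that most exclusions will come from the individualised arm, or that this arm will consist mostly of infants enrolled in physiotherapist hours. The article says only that exclusions there are more likely, and on occasions. A reader might also take the comparison with control as the leading one, but the article lists three primary tests without ranking them. Nor does it report that any such exclusion has occurred.

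**Conclusion.** The concern holds for bias. As written, the plan permits exclusions after randomisation that depend on the allocated arm, leaves those infants out of the primary analysis, and offers as remedy an allowance that cannot address selection. Both comparisons involving the individualised arm are exposed. This rests on the text alone.

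The size does not. Frequency, prognostic difference and direction are all unknown, so the type I error of 0.04 to 0.08 is an illustration that depends on an assumed residual bias of 0.4 to 0.6 points. The effect on power is modest and arises only if the individualised arm loses more than 20%.

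**What to change.** 1. Reconcile Interventions, Statistical and sample size calculations, and Discussion. State that physiotherapist absence is not a reason to exclude a randomised infant or to stop collecting the 24 h index, and that every randomised infant with 24 h data is analysed in the allocated arm.
2. Remove the statement that the drop-out allowance compensates for these exclusions.
3. Report any exclusions of this kind that have already occurred, by arm and time of enrolment, and restore those infants to the primary analysis where 24 h data exist. Whether all parts of the index, oral intake over 24 h included, can be recovered is not known from the article.
4. Optionally, for remaining enrolment, confirm before an envelope is opened that all three arms can be delivered, so that any restriction falls equally on them.

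Items 1 and 2 cost a change of wording and continued assessment of a few infants on the ward's existing three-hourly schedule. The effect estimate will then include infants who missed the session, which fits the stated pragmatic aim. Item 4 means that some off-hours infants are not enrolled, which narrows the population. It also cannot reach infants enrolled since recruitment began in November 2017.
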